### Safety evaluation

Safety evaluation encompasses continuous monitoring of vital signs throughout the study period, as well as the systematic observation and documentation of all adverse events (AEs) and serious adverse events (SAEs). AE is defined as any untoward medical occurrence in a patient administered the study drug, which may present as symptoms, signs, illness, or laboratory abnormalities, regardless of a causal relationship with the study drug. SAE is defined as any untoward medical occurrence that occurs after administration of the study drug and results in one or more of the following outcomes: death, life-threatening condition, persistent or significant disability or incapacity, hospitalization or prolongation of existing hospitalization, or congenital anomaly or birth defect. Particular attention will be directed toward electrolyte-related adverse events, including QT interval prolongation, cardiac arrhythmias, and neuromuscular manifestations such as hyperreflexia, muscle cramps, or tetany, which will be systematically recorded and analyzed. All adverse events are to be managed promptly upon detection. Any serious adverse event must be reported to the clinical trial site and the institutional ethics committee within 24 h of awareness.

### Estimation of sample size

The sample size estimation is based on a non-inferiority design. According to previous findings and literature reports (Liu et al., 2018), nalbuphine is capable of maintaining the target analgesic effect within 3–24 h post-administration, with CPOT scores ≤2 for more than 70% of the time. An analgesic success rate approaching 100% is anticipated. We estimate an efficacy of 99% in the experimental group, and the control groups. Following consultation of several experts, the non-inferiority margin δ is set at −8%, meaning that an 8% reduction in efficacy representing the maximum clinically acceptable difference. A two-sided significance level of α = 0.05 and a power of 80% (β = 0.2) are applied. Sample size estimation is conducted using the Farrington and Manning method via PASS 2022 software, assuming a 1:1 allocation ratio between the two groups, and 73 participants per group is required. Assuming an anticipated dropout rate of approximately 12%, a total of 168 subjects is needed.

### Statistical analysis

Statistical analyses will be performed using SAS software (version 9.4 or higher). Continuous variables will be presented as mean ± standard deviation for normally distributed data and median ± interquartile range for non-normally distributed data, whereas categorical variables will be summarized as frequencies and percentages. All statistical tests and confidence intervals (CI) will be two-sided, with statistical significance defined as a p-value less than 0.05. The difference in analgesic success rates between the experimental and control groups will be estimated using the Miettinen and Nurminen method to calculate the two-sided 95% CI. Non-inferiority will be established if the lower bound of this interval exceeds −8%. The proportion of time during which patients maintain a CPOT score ≤2 and a RASS score between −2 and +1 will be analyzed using the arcsine square root transformation, followed by between-group comparison via the t-test. Time from initiation of study drug to successful weaning and time to ICU discharge will be illustrated using Kaplan-Meier survival curves and compared using the log-rank test. The frequency and dosage of rescue propofol sedation, along with total propofol dose administered, will be compared between groups using either the t-test or Wilcoxon rank-sum test, depending on data distribution. The proportions of patients requiring concomitant propofol sedation, weaning success rate, and ICU discharge rate will be compared using the χ^2^ test or Fisher’s exact test. The incidence of adverse events will also be assessed using χ^2^ test or Fisher’s exact test.

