### Participants

Inclusion criteria are: 1) age ≥18 years and ≤80, 2) ICU patients who are intubated are expected to require mechanical ventilation for more than 6 h, 3) patients or their guardians have a full understanding of the purpose and significance of this trial, and voluntarily participate in this clinical trial and sign an informed consent form.

Exclusion criteria are: 1) allergy or unsuitability to any composition of study drugs or propofol, 2) life expectancy of less than 48 h, 3) neurological disorder and any other condition interfering with sedation assessment, 4) gastrointestinal obstruction, 5) asthmatic, 6) abdominal compartment syndrome, 7) serious hepatic dysfunction (Child-Turcotte-Pugh score 10–15), 8) acute kidney injury (KDIGO stage 2 or 3) or chronic kidney disease with glomerular filtration rate (GFR) < 29 mL/min/1.73 m^2^, 9) circulatory instability (the need for a continuous infusion of norepinephrine at ≥ 0.5 ug/kg/min to maintain proper blood pressure), 10) a need of deep sedation (RASS score −4 or −5) or paralytics, 11) anticipation to receive operations (including tracheotomy), 12) abuse of controlled substances or alcohol, 13) pregnancy, lactation, or an intention of gestation in 6 months, 14) inclusion in another interventional trial in the past 30 days, 15) other conditions deemed unsuitable to be included.

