### Outcomes

The primary outcome is the analgesic success rate during 24 h of study drug administration. Analgesic success is defined as the fulfillment of both criteria: 1) no administration of rescue analgesic medication, and 2) maintenance of a CPOT score ≤2 for at least 70% of the observation period during study drug infusion.

The secondary outcomes include: 1) The percentage of time within CPOT score ≤2 and RASS score between −2 and +1 during 24 h of study drug administration: This metric represents the proportion of time during which a patient maintains a CPOT score of ≤2 and a RASS score between −2 and +1, relative to the total duration of study drug administration. 2) The frequency and dosage of rescue sedation during 24 h of study drug administration: The frequency refers to the number of rescue sedative administrations, while the dosage indicates the total amount of propofol administered as rescue sedation during the infusion of the study drug. 3) The proportion of patients requiring rescue sedation during 24 h of study drug administration: This is the percentage of patients in each treatment group who received concomitant propofol for rescue sedation during study drug infusion, calculated as (Number of patients receiving propofol/Total number of patients in the group) × 100%. 4) The total cumulative dose of rescue sedative during 24 h of study drug administration: The sum of all propofol doses administered as rescue sedation during the period of study drug infusion. 5) The time to successful weaning and ICU discharge during 24 h of study drug administration: Time to successful weaning is defined as the interval from the initiation of the study drug to liberation from mechanical ventilation. Time to ICU discharge is defined as the interval from study drug initiation to actual ICU discharge. Successful weaning is achieved when the patient is extubated and subsequently maintains stable spontaneous breathing without the need for reintubation. 6) The weaning success rate and the proportion of patients discharged from the ICU: The weaning success rate reflects the percentage of patients successfully weaned from mechanical ventilation. The proportion of patients discharged from the ICU indicates the percentage of patients transferred out of the ICU within the observation period.

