Daily records include cumulative sedative and analgesic doses, time to successful weaning, and ICU discharge time. All adverse events and concomitant medications are systematically recorded throughout drug administration and within 12–48 h after drug discontinuation. A trained investigator at each study center is responsible for the daily screening and enrollment of patients, ensuring strict adherence to the study protocol, and completing the electronic case report form (e-CRF). All data are handled with confidentiality and anonymized to protect patient identity. Access to data is restricted to authorized personnel only. Data accuracy is subject to periodic monitoring and verification by the principal investigator to ensure compliance with regulatory and quality standards.

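### Kaplan-Meier curves are planned for weaning and ICU discharge with no rule for deaths; if deaths are censored, the curves overstate both, probably by a small amount

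*Protocol article*

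**What the plan says.** All references are to the protocol article.

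- **Method.** Under Statistical analysis, the times from study drug start to successful weaning and to ICU discharge "will be illustrated using Kaplan-Meier survival curves and compared using the log-rank test".
- **Definitions.** Under Outcomes: "Time to successful weaning is defined as the interval from the initiation of the study drug to liberation from mechanical ventilation", and "Time to ICU discharge is defined as the interval from study drug initiation to actual ICU discharge". Both are favourable events.
- **Window.** The same outcome is headed "The time to successful weaning and ICU discharge during 24 h of study drug administration", which does not sit easily with an interval that ends at actual discharge.
- **Observation.** Under Data collection and management: "All adverse events and concomitant medications are systematically recorded throughout drug administration and within 12–48 h after drug discontinuation". Table 1 places the outcome variables at the same close-out visit. The daily records also list ICU discharge time.
- **Death.** Under Safety evaluation, death appears as one of the outcomes that make an event serious ("results in one or more of the following outcomes: death, life-threatening condition"). Under Participants, patients with "life expectancy of less than 48 h" are excluded. Death is not mentioned in connection with the two time-to-event outcomes.
- **Companion proportions.** The "weaning success rate, and ICU discharge rate will be compared using the χ^2^ test or Fisher’s exact test".

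**The concern.** A ventilated ICU patient who dies can no longer be weaned or leave the ICU alive, so death is a competing event for both outcomes. A Kaplan-Meier analysis that censors patients at death treats them as if they could still have the event later. One minus the curve then estimates weaning or discharge in a hypothetical setting without deaths, not the share of patients who are actually weaned or discharged.

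Two things are at stake. A reader who takes the curve as a probability is given too high a figure. The report would also contain two figures for the same event at the same time, one from the curve and one from the planned proportion, that disagree for no clinical reason.

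**Working it through.** **Plan's own figure.** There is none to reproduce. The article gives no rate of death, weaning or discharge, and the sample size calculation does not use these outcomes.

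**Length of the scheduled window.** Infusion lasts up to 24 h and close-out falls 12–48 h after it ends. For a full infusion, scheduled contact therefore ends between 24 + 12 = 36 h and 24 + 48 = 72 h after drug start. It ends earlier where the infusion stops early for a weaning trial.

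**Model.** Let w be the true cumulative incidence of the favourable event at the horizon and d that of death. Assume constant cause-specific hazards and no other censoring.

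- Total cumulative hazard: −ln(1 − w − d).
- Part due to the favourable event: the fraction w/(w + d) of that total.
- With deaths censored at death, 1 − KM = 1 − (1 − w − d)^(w/(w + d)).

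**Two examples.**

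- w = 0.30, d = 0.01: −ln(0.69) = 0.3711; times 0.30/0.31 = 0.3591; 1 − exp(−0.3591) = 0.302. Excess 0.2 points.
- w = 0.70, d = 0.05: −ln(0.25) = 1.3863; times 0.70/0.75 = 1.2939; 1 − exp(−1.2939) = 0.726. Excess 2.6 points.

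**Range.** Excess of 1 − KM over the true incidence, in percentage points. All death rates are assumptions.

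| True incidence | 1% deaths | 2% | 5% | 10% | 20% |
|---|---|---|---|---|---|
| 30% | 0.2 | 0.3 | 0.9 | 1.8 | 4.0 |
| 50% | 0.3 | 0.6 | 1.6 | 3.4 | 7.7 |
| 70% | 0.5 | 1.0 | 2.6 | 5.5 | 13.3 |

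The 1–5% columns are the range assumed for a window of at most about 72 h. The 10–20% columns show what would follow from longer follow-up or a sicker population.

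**Alternative handling.** If patients who die stay in the risk set as non-events to a common horizon, and there is no other censoring, the estimate at that horizon is simply the proportion with the event. The excess is then zero.

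**Scale.** With 168/2 = 84 patients per arm, the standard error of a proportion of 60% is √(0.60 × 0.40/84) = 0.053, or 5.3 points.

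**The case against.** The strongest reply is that the article names a method and not a censoring rule. Kaplan-Meier with deaths carried to a common horizon as non-events has no such bias, and a censoring rule for secondary outcomes is normally left to the full protocol or SAP, neither of which is shown. This stands as far as certainty goes: a reader might infer that the curves will overstate weaning and discharge, but the article supports that only if deaths are censored at death. It does not dispose of the point. The choice of Kaplan-Meier is stated, its usual default is the problematic one, and a better display is available at little cost.

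The second reply is size. The exclusion of patients with short life expectancy, high vasopressor need, severe liver dysfunction or moderate to severe kidney injury should make early deaths few, and an excess of up to 2.6 points is within sampling error. This also stands, though the excess is systematic and would not average out. A reader might picture follow-up of several weeks and an error above ten points. The article states no such horizon, and its scheduled contact ends by about 72 h.

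Two further inferences are not supported:

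- **An arm with more deaths would look faster to wean.** That needs the patients who die to be those least likely to wean. The calculation above assumes equal hazards for all patients, so it does not show this, and the article gives no data on it.
- **The log-rank test is invalid.** With deaths censored, it remains a valid comparison of cause-specific hazards. Preferring Gray's test is a choice of estimand.

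Finally, the planned proportions do not share the bias. This limits the harm, but it is also why the curves and proportions would disagree.

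**Conclusion.** The point holds in conditional form and is minor. The plan fixes Kaplan-Meier curves for two events that death precludes and does not say how deaths are treated. If deaths are censored at death, one minus the curve overstates the probability of weaning and of discharge. The excess is about 0.2–2.6 percentage points at true incidences of 30–70%, and it reaches about 2–13 points only with 10–20% deaths. These sizes rest on assumed mortality and constant hazards; the direction does not depend on the particular rates, provided that some deaths occur while others can still have the event.

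The horizon is a related gap: the outcome is headed as a 24 h measure but defined up to actual discharge, so the article does not settle which deaths matter. The primary non-inferiority analysis and the sample size are untouched.

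**What to change.** 1. Replace the Kaplan-Meier curves for both outcomes with Aalen-Johansen cumulative incidence curves, with death as a competing event. Alternatively, keep patients who die in the risk set as non-events to one fixed horizon common to all patients.
2. State that horizon, and reconcile the 24 h heading with the definition that runs to actual discharge. With complete follow-up to the horizon, the curves will then agree with proportions taken at the same time.
3. Keep the log-rank test if wanted, labelled as a comparison of cause-specific hazards. Gray's test is optional.

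**Cost.** Within the scheduled window this is a change of wording and minor analysis work, since deaths up to close-out are captured as serious adverse events. Close-out can fall as early as 12 h after the drug ends, so a horizon beyond a patient's close-out also needs vital status and event times collected to that horizon. The change is best made before outcome data are seen.

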## Methods

### Study design

This is a multicenter, randomized, single-blind, parallel, positive control study initiated by Yichang Humanwell Pharmaceutical Co., Ltd., China. Apart from our ICU, 15 ICUs from tertiary hospitals in China enroll patients in the trial. This study was registered at ClinicalTrials.gov (NCT06785571). The trial protocol is reported in accordance with the Standard Protocol Items: Recommendations for Interventional Trials (SPIRIT) guidelines (Calvert et al., 2018). Table 1 presents the scheduled process of enrollment, interventions, and measurements.

**TABLE 1 T1:** Scheduled process of enrollment, interventions, and measurements.

Timepoint	Study period				
	Enrollment	Allocation	Post-allocation		Close-out
	After admission to ICU	After obtaining informed consent	Before study drug administration	Study drug administration	12–48 h after study drug administration ended
Enrollment					
Eligibility screen	X	​	​	​	​
Informed consent	X	​	​	​	​
Allocation	​	X	​	​	​
Interventions					
Nalbuphine hydrochloride	​	​	​	X	​
Hydromorphone hydrochloride	​	​	​	X	​
Assessments					
Baseline variables	X	​	​	​	​
Vital signs	X	X	X	X	X
RASS score	X	X	X	X	​
CPOT score	X	X	X	X	​
Laboratory tests	X	​	​	​	X
APACHE II score and SOFA score					
Dose of drugs (study drugs, analgesics, vasopressors, rescue sedatives)	​	​	​	X	​
AEs and SAEs	​	​	​	X	​
Outcome variables	​	​	​	​	X

RASS, Richmond Agitation–Sedation Scale; AEs, adverse events; SAEs, serious adverse events.

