### Data collection and management

Upon enrollment, detailed patient demographic data (age, sex, body weight, ethnicity), medical history, clinical data (vital signs, ECG, laboratory tests), and comorbidities are collected. Vital sign monitoring includes heart rate, systolic and diastolic blood pressure (SBP/DBP), respiratory rate, and peripheral capillary oxygen saturation (SpO2). These parameters are recorded immediately at the initiation of the study drug administration (designated as T0), with subsequent assessments performed every 20 min during the first 2 h post-administration. From 2 to 24 h post-administration, or when weaning screening criteria are met and a weaning trial is planned, recordings are taken every 2 h. Additional recordings are obtained immediately following successful weaning and/or ICU discharge. Body temperature is recorded at T0 and again at 24 h post-administration or when weaning criteria are met. Continuous ECG monitoring is conducted throughout the study drug administration. Standard 12-lead ECG is obtained, and blood samples (for complete blood count, biochemistry, coagulation profile, and pregnancy test when applicable) are collected before randomization and within 12–48 h after discontinuation of the study drugs.

The CPOT and RASS scores are evaluated as baseline assessments prior to randomization. Routine evaluations are performed immediately after T0 and every 2 h thereafter. Prior to any dose adjustment, both scores are documented. After each adjustment, assessments are repeated every 5 min until clinical targets are met and no further dose modifications are needed. If the patient is in undisturbed sleep, the RASS score is recorded as unchanged from the previous value and annotated as “sleeping”. However, for final determination of titration cessation, patients are awakened for formal CPOT and RASS evaluation.

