### Limitations

Despite these strengths, several limitations merit consideration. First, although nalbuphine exhibits a ceiling effect for analgesia, this occurs at doses exceeding 0.4 mg/kg, which are not reached in our protocol (maximum 10 mg loading plus 5 mg/h maintenance). Within the selected dose range, dose-dependent analgesic efficacy is preserved. Nevertheless, the ceiling effect may limit efficacy in patients with very high opioid requirements, which we have acknowledged as a study limitation. Second, one limitation of our study is the lack of precise equipotent dosing between nalbuphine and hydromorphone. The chosen dose ratio (approximately 4:1) may underestimate nalbuphine’s required dose if the true potency ratio is 5-7.5:1. To mitigate this, our protocol permits supplemental boluses and upward titration to a maximum of 5 mg/h. Moreover, we will conduct sensitivity analyses using alternative potency assumptions to assess the robustness of the non-inferiority conclusion. Future dose-optimization studies in ICU patients are warranted. Third, the protocol, as described, may face challenges related to generalizability. ICUs are highly heterogeneous (Zimmerman et al., 2006), and patient populations can vary significantly between centers in terms of primary diagnoses (e.g., medical, surgical, or trauma), severity of illness, and baseline organ function. If the inclusion and exclusion criteria are too restrictive, the results may not be applicable to all subtypes of critically ill patients. Additionally, the findings will be directly comparable only to the specific positive-control analgesic chosen, conclusions may not extend to all opioids or analgesics used in the ICU. The single-blind design carries an inherent risk of assessment bias despite mitigation strategies, and the exclusion of patients with severe organ dysfunction, hemodynamic instability, or need for deep sedation further limits generalizability to the sickest ICU subpopulations. Variability in patient pharmacodynamics—especially in those with organ dysfunction, comorbidities, or concurrent sedative use—may also influence analgesic response. Moreover, the 24-h intervention period may not capture longer-term outcomes such as delirium, opioid withdrawal, or post-ICU dependence, and variations in institutional sedation protocols and nursing expertise could influence implementation fidelity across centers. These factors should be considered when interpreting results and may inform future research aimed at optimizing dosing strategies or evaluating specific subgroups.

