
To maximize clinical utility, prespecified subgroup and sensitivity analyses are necessary. Subgroup analyses stratified by baseline hepatic function (e.g., Child-Pugh class) and renal function (e.g., KDIGO stage) would assess whether nalbuphine’s noninferiority is maintained across the spectrum of organ dysfunction severity. Sensitivity analyses adjusting for key potential confounders—including illness severity (e.g., APACHE II score), concomitant sedative use, and delirium status—would further enhance the robustness and generalizability of the primary findings. Although these analyses are exploratory, they are valuable for generating new research ideas and guiding personalized pain management in critically ill patients.

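### Time to weaning and time to ICU discharge have only an unadjusted log-rank comparison, which is valid but may give up power that a supportive severity-adjusted Cox model could recover

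*Protocol article*

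**What the plan says.** - **Test.** Statistical analysis: the two times "will be illustrated using Kaplan-Meier survival curves and compared using the log-rank test". No covariate or stratification factor is named. All tests "will be two-sided, with statistical significance defined as a p-value less than 0.05".
- **Rank.** Outcomes: the two times form secondary outcome 5, titled "The time to successful weaning and ICU discharge during 24 h of study drug administration". The definitions under that title run from study drug start to liberation from the ventilator and to actual ICU discharge.
- **Severity scores.** Study design, Table 1 has a row "APACHE II score and SOFA score", with no time point marked in the text as extracted. Data collection and management lists demographics and then says "medical history, clinical data (vital signs, ECG, laboratory tests), and comorbidities are collected"; no severity score is named there.
- **Expected variation.** Limitations: patient populations may differ between centers in diagnosis, "severity of illness, and baseline organ function".
- **Adjustment elsewhere.** Limitations also mentions exploratory sensitivity analyses of the primary findings that adjust for confounders, "including illness severity (e.g., APACHE II score), concomitant sedative use, and delirium status". The wording is conditional and does not mention the two time-to-event outcomes.
- **Power.** Estimation of sample size: "A two-sided significance level of α = 0.05 and a power of 80% (β = 0.2) are applied". This concerns the analgesic success rate only.

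**The concern.** Time to weaning and time to ICU discharge can be expected to depend on how ill the patient is at entry. When a strong prognostic factor is left out of a time-to-event comparison, the marginal hazard ratio moves towards 1 and the log-rank test loses power relative to a model that includes the factor. The article itself expects a wide spread of severity, appears to schedule two severity scores, and names APACHE II as a variable worth adjusting for.

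It raises that adjustment only for the primary findings, where 99% success is expected in both arms. That is about 168 × 0.01 ≈ 2 failures, so a covariate has almost nothing to explain. Weaning and discharge may have many more events. At stake is the precision of two secondary comparisons, and whether a reader gets an effect size with them: the log-rank test alone gives only a p-value.

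**Working it through.** **1. The plan's own figure.** No figure is stated for these two outcomes. The only sample size is for the primary outcome, and it reproduces. The Farrington-Manning method with 99% in both arms and a margin of 8 points gives constrained null rates of 0.9149 and 0.9949.
- s0 = √(0.9149×0.0851 + 0.9949×0.0051) ≈ 0.288
- s1 = √(2×0.99×0.01) ≈ 0.141
- n = [(1.96×0.288 + 0.842×0.141)/0.08]² ≈ 72.9, so 73 per group

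With 12% dropout, 73/0.88 rounds up to 83 per group, or 166 in total, against 168 stated. The present point touches neither figure.

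**2. Assumed inputs.** None of these comes from the article except the total of 168.
- 84 per arm, exponential times, control median 36 h, hazard ratio 1.5.
- One standard-normal severity score that changes the hazard 1.3-, 1.6- or 2-fold per SD.
- Two windows: 24 h, from the outcome's title, and 72 h, the longest the schedule allows (24 h of drug plus a close-out at up to 48 h).

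**3. Benchmark without any severity effect.** The event fraction by time w is 1 − 2^(−w/36) in controls and 1 − 2^(−1.5w/36) in the other arm. Schoenfeld power is Φ(½√D × ln 1.5 − 1.96).
- 24 h: D = 84 × (0.370 + 0.500) ≈ 73. Power = Φ(4.275×0.4055 − 1.96) = Φ(−0.23) ≈ 41%.
- 72 h: D = 84 × (0.750 + 0.875) ≈ 136.5. Power = Φ(5.842×0.4055 − 1.96) = Φ(0.41) ≈ 66%.

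**4. Simulated power, unadjusted vs adjusted for the score.** The second figure in each cell is from a repeat with 4,000 simulated trials per setting.

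| Hazard change per SD | 24 h | 24 h, repeat | 72 h | 72 h, repeat |
|---|---|---|---|---|
| 1.3-fold | 37 vs 39% | 40 vs 40% | 63 vs 65% | 63 vs 66% |
| 1.6-fold | 38 vs 44% | 39 vs 41% | 55 vs 64% | 54 vs 62% |
| 2-fold | 32 vs 40% | 35 vs 43% | 46 vs 63% | 47 vs 63% |

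Other runs of the same 72 h setting gave gains of up to 18 points (for example 47 vs 65% at 2-fold). The gain is therefore about 2 points, or nothing, with a weak score. With a strong one it is about 9 points at 24 h and about 18 at 72 h. Adjusted power stays near the benchmark in step 3, while unadjusted power falls below it.

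**5. Different assumptions.** 146 patients (2 × 73), hazard ratio 1.6, severity hazard ratio per SD of 1.0 / 0.8 / 0.67 / 0.5. Log-rank vs adjusted Cox:
- 30% events: 34 vs 34, 34 vs 34, 31 vs 30, 30 vs 33%
- 60% events: 57 vs 57, 57 vs 58, 55 vs 58, 46 vs 58%
- 90% events: 77 vs 76, 73 vs 76, 68 vs 76, 56 vs 76%

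At 30% events there is no clear gain. At 90% events with the strongest score it is 20 points. Where adjustment does not help, it costs at most about 1 point, which is within simulation error.

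**6. Validity.** With no treatment effect, the log-rank test in the step 5 setting rejected in 4.3% to 5.6% of trials at every score strength.

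**The case against.** The strongest reply is that nothing here is an error. An unadjusted log-rank test is a legitimate choice in a randomized trial, the outcomes are secondary with no stated power, and a supportive adjusted model is the kind of detail a condensed article may leave to an SAP that is not shown. All of this stands. It makes the point an optional improvement, and if the SAP already has such a model, confirming it is enough.

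The size is also open to challenge. Hazard ratio, median, event fraction and score strength are all assumed, and the 72 h window is the favorable one. That stands too, which is why both windows and the weak-score case are shown.

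Several stronger readings are tempting, but the article does not support them:

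- **That power is given up for certain and at no saving.** The loss can be negligible. The log-rank test also avoids a covariate model, a missing-score rule and a conditional estimand.
- **That a chance severity imbalance undermines the comparison.** The test's error rate already allows for chance imbalance (step 6). That the randomization text names no stratification factor does not change this.
- **That a usable baseline score exists for every patient.** The Table 1 row shows no time point, which may be a loss in text extraction, and the data collection text names no score. Availability has to be confirmed.
- **That the article reserves APACHE II adjustment for the primary outcome.** The Limitations passage is conditional and exploratory, and it does not exclude adjusting other outcomes.

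**Conclusion.** The point holds as an efficiency suggestion for two secondary outcomes. The planned test is valid but unadjusted, and the article gives its own reasons to think that severity matters. Under the assumptions in step 2, a severity-adjusted model gains about 2 to 9 points of power with a 24 h window and about 2 to 18 points with a 72 h window, depending on how prognostic the score is. With a weak score or few events the gain is little or nothing. At 24 h the comparison has low power either way, at about 44% or less. No single figure can be given, because the article states no hazard ratio, event fraction or score strength. A reader might infer that the trial's main result is weakened; it is not, since the primary non-inferiority comparison and its sample size do not depend on this test.

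**What to change.** Before unblinding, add to the SAP, for both outcomes, a Cox model with treatment and pre-allocation APACHE II (or SOFA, one of them chosen in advance) as a continuous covariate. Report the hazard ratio with its 95% CI and keep the log-rank test beside it. State a rule for missing scores and a check of proportional hazards. Mark in Table 1 when the score is taken, and confirm that this is before allocation.

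The cost is a few lines of SAP text and, if needed, one schedule entry. The main downside is interpretive: the adjusted hazard ratio is conditional on severity and will generally differ from the unadjusted one, so the unadjusted hazard ratio should be shown as well.
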